**Methods/design:**

This prospective, longitudinal cohort study will be incorporated in the usual care of patients with adolescent idiopathic scoliosis. All new patients between 8 and 17 years with adolescent idiopathic scoliosis (Cobb angle >10 degrees) visiting the outpatient clinic of the University Medical Center Groningen are included in this study. Follow up will take place every 6 months. The present study will use a new ultra-low dose X-ray system which can make total body X-rays. Several maturity indicators are evaluated like different body length dimensions, secondary sexual characteristics, skeletal age in hand and wrist, skeletal age in the elbow, the Risser sign, the status of the triradiate cartilage, and EMG ratios of the paraspinal muscle activity.

Correlations of all dimensions will be calculated in relationship to the timing of the pubertal growth spurt, and to the progression of the scoliotic curve. An algorithm will be made for the optimal treatment strategy in the individual patient with adolescent idiopathic scoliosis.

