The peak growth spurt is known to take place between 10 and 14 years in 95% of the girls, and between 12 and 16 years in 95% of the boys[8,9]. This range holds for a large population, but is too wide to make accurate predictions in the individual patient. However, several other maturity indicators are related to the pubertal growth spurt. Maturity is multidimensional and has various components, including chronological age, skeletal age in different areas, the Risser sign, status of the triradiate cartilage, Tanner stage of sexual maturation, age at thelarche and menarche, and several length dimensions like sitting height, subischial leg length, and foot length or shoe size. These indicators of maturity are all signs that reflect growth or remaining growth of the patient and can be useful in predicting timing of the pubertal growth spurt or peak growth velocity of total body height in the individual patient.

Researchers have tried to find different ways to predict curve progression in AIS as well, besides relating progression to the peak growth velocity of height. A promising method was shown by Cheung et al[3,10], who found a relationship between curve progression and altered electromyography ratios of the convex and concave sides of the curve. Enhanced EMG ratios were observed at three levels of the scoliotic curve (lower end vertebra, apex, and upper end vertebra) at the start of progressive periods. At the start of a non-progressive period, such an enhanced EMG ratio was only observed at the level of the apex vertebra[3].

Only few studies have investigated maturity indicators in patients with idiopathic scoliosis[11-14]. Moreover, studies have compared only some of these indicators, and only either in relationship to the peak growth velocity of total body height, or to curve progression, not to both in one study. Results of different studies are contradictory and inconsistent, so therefore a good algorithm for determining treatment options in AIS is still lacking.

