### Identification and recruitment of study participants

Patients between 8 and 17 years old, visiting the outpatient clinic of the UMCG with adolescent idiopathic scoliosis will be participating in this study. The Cobb angle should be >10 degrees, measured by an experienced observer on an AP X-ray of the total spine.

Patients should not have had previous spinal surgery; there should be no evidence of neuromuscular disease or skeletal dysplasia, and no evident abnormalities of maturation or height. Furthermore, patients with mental incapacitation are excluded since this can influence the reliability of the measurements in the way that these patients most often can not stand still during the height measurements and EMG measurements. Patients are excluded as well when they are participating in a different study simultaneously.

The assessment to include or exclude a patient will be determined by the orthopaedic surgeon. All patients who meet the inclusion criteria will be asked to participate in this study and give their informed consent.

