### Physical examinations

Regular physical exam of the back is done including inspection, determination of the range of motion, and the Adam's forward bending test.

Measurements are taken for total height, sitting height, lateral arm span, foot length, shoe size, and weight. Subischial leg length is calculated by distracting sitting height from total height. All length measurements are measured three times per visit, to the nearest mm, and an average will be calculated.

Measurement of total height is done by use of a stadiometer constructed according to the internationally agreed assignments and with digital reading. The patient is asked to stand upright with bare feet, having their feet parallel together, and the back of the head touching the upright steel rod against the wall. The child is encouraged to stretch out to the maximum by applying gentle pressure upward under the mastoid process, with the recorder watching to see that the heels are not off the ground. The recorder measures height by lowering the horizontal bar of the stadiometer, making contact with the top of the head. No height corrections are made for curve magnitude.

Sitting height is measured with similar height measuring equipment, while the patient sits on a table with exact known height. The patient is asked to sit straight and the legs hanging freely from the ground. Furthermore, measurement of sitting height is similar to the measurement of total height.

Lateral arm span is measured using a tape measure, from the end of the long finger of one hand, to the end of the long finger on the other hand, with arms maximally outstretched. The tape measure is confirmed to the wall, and the patient is asked to stand straight against the wall and stretch out the arms horizontally.

Foot length and shoe size are measured with a validated calliper in which length in mm and standardized shoe size can be determined. Each patient's bare left and right foot are measured individually while standing full weight bearing. The patient stands in the calliper with the back of the heel against the stationary arm, and the movable arm is brought into contact with the tip of the longest toe. The length is measured to the nearest mm, and shoe size to the nearest half-size.

Weight is measured on a validated scale to the nearest 0.1 kg.

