### Outcome measurements

Longitudinal data will be acquired for:

• Scoliotic curve progression (in degrees Cobb angle)

• Height, and growth velocity of height

• Sitting height, and growth velocity of sitting height

• Leg length, and growth velocity of leg length

• Foot length, shoe size, and growth velocity of foot length and shoe size

• Weight, and growth velocity of weight

• Spinal length, and growth velocity of spinal length

• Tanner stage of secondary sexual characteristics

• Riser sign and status of the triradiate cartilage

• Skeletal age in hand, wrist, and elbow

• EMG ratios of the paraspinal muscles

Finally, an algorithm will be developed for predicting peak growth velocity of height and curve progression in individual patients with adolescent idiopathic scoliosis (see Figure 4). 

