### Sample size and statistical analysis

The maximum sample size of this study is not determined on beforehand, as the study is aimed to proceed for the coming years.

We aim to perform a first preliminary analysis of the longitudinal data when patients have a follow up of at least 2 years. As the expected number of new patients is 60 each year, it will take 2.5 years for 30 patients to reach a follow up of at least 2 years. Taking a loss to follow up into account due to surgical treatment, we expect to be able to analyse the complete data of at least 25 patients. The statistical power will increase with a longer follow up and more patients. The number of 25 patients was checked whether it was large enough to obtain a good prediction model according to the criteria of Knofczynski and Mundfrom [33]. With a significant large influence of 4-5 predictor variables (as is expected in this study) and a squared multiple correlation coefficient between 0.5 and 0.7 between 25 and 65 patients should be included. Therefore the first preliminary analysis will be performed using data of 25 patients.

Individual data charts are made, and results of each parameter are plotted against the growth velocity of total body height and the curve progression.

All statistical calculations are made using SPSS (SPSS Inc, Chicago USA). Pearson correlation coefficients are computed for each individual possible related parameter against the peak growth velocity and the curve progression (Figure 5). A correlation above 0.70 is believed to be clinically relevant. To be able to interpret this value in a reliable way, we will report the confidence intervals as well.

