**Figure 5 F5:**
[figure not shown]
**Correlations investigated in this study**.

Multiple linear regression analysis of the data is used to determine predictive equations for the timing and magnitude of the peak growth velocity of height, and the scoliotic curve progression.

Missing data concerning individual parameters are not expected in this study. I.e. when a patient misses his or her follow up consult, *all *parameters will be missing and therefore no correlations can be calculated for that time point. It is not expected that when a patient does come to the outpatient clinic, for example the sitting height will not be measured and all the other parameters will be measured. If it does happen anyway that one individual parameter is missing, imputation techniques will be applied during data analysis.

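### The 0.70 correlation cutoff does not measure prediction in the individual patient: its meaning changes with the age spread of the sample and with an outcome that the analysis section leaves open

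*Protocol article*

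**What the plan says.** All places are in the protocol article.

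- **Rule** (Sample size and statistical analysis): "Pearson correlation coefficients are computed for each individual possible related parameter against the peak growth velocity and the curve progression", followed by "A correlation above 0.70 is believed to be clinically relevant". Confidence intervals are to be reported. No derivation of 0.70 is given, and no error in years or degrees.
- **Outcome:** the rule refers to peak growth velocity without saying which aspect. The Abstract has "Correlations of all dimensions will be calculated in relationship to the timing of the pubertal growth spurt". The regression paragraph of the statistical section names both timing and magnitude.
- **Goal and use:** the Background sets prediction of timing in the individual patient as the goal. The Abstract's discussion and the closing Discussion say that clinicians can pick indicators from the single correlations.
- **Population** (Identification and recruitment of study participants): "Patients between 8 and 17 years old, visiting the outpatient clinic of the UMCG".
- **Benchmark** (Background): 95% of girls peak between 10 and 14 years and 95% of boys between 12 and 16. The protocol comments: "This range holds for a large population, but is too wide to make accurate predictions in the individual patient".
- **Parts of height** (Physical examinations): "Subischial leg length is calculated by distracting sitting height from total height". Outcome measurements lists "Leg length, and growth velocity of leg length" and the same pair for sitting height.

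**The concern.** A Pearson correlation is a ratio of spreads. Maturity indicators rise with age, so a sample covering many years of age gives large coefficients against time to peak even when individual error is large, and a narrow sample gives small ones for the same error. A fixed cutoff therefore does not correspond to any fixed precision. If the outcome is age at peak, the problem reverses: an indicator that tells exactly how far the child is from the peak correlates poorly, because visit age has not been taken out.

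A clinician reading that an indicator exceeds 0.70 could take it as fit for the individual patient when it does worse than knowing the child's age, and could discard an informative one. Sitting height and leg length raise a second issue: each is part of height, so their concurrent velocities are part of the outcome they would be correlated with.

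**Working it through.** **The plan's own figure.** The 0.70 is asserted, so there is nothing to reproduce. The accrual figure in the same section does reproduce: 60 per year × (2.5 − 2) years = 30 patients with two years of follow-up.

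**Inputs.**
- SD of age at peak within one sex: a 95% range of 4 years, if normal, gives 2/1.96 = 1.020 years.
- SD of age: 9/√12 = 2.598 years, if ages are uniform over 8-17 (assumption; no age distribution is given).
- Time to peak = age at peak − current age, with the two independent and every peak known (assumptions). Its SD is √(2.598² + 1.020²) = 2.791 years.

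Correlations are given as absolute values.

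**1. What 0.70 leaves.** The 95% half-width is 1.96 × SD of outcome × √(1 − r²).
- Outcome time to peak: 1.96 × 2.791 × √0.51 = ±3.9 years.
- Outcome age at peak, one sex: 1.96 × 1.020 × √0.51 = ±1.4 years.

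The same 0.70 stands for two very different precisions.

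**2. Chronological age as benchmark against time to peak.** r = SD(age)/√(SD(age)² + SD(peak)²).
- One sex: 2.598/2.791 = 0.93.
- Both sexes together, 80% girls (assumption), means two years apart: SD(peak) = √(1.020² + 0.8 × 0.2 × 2²) = 1.297, so r = 2.598/√(2.598² + 1.297²) = 0.89.
- Error left by age, one sex: 1.96 × 1.020 = ±2.0 years, the range that the Background rejects.

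Under these assumptions an indicator must exceed about 0.93 merely to beat age.

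**3. How far the benchmark moves with the sample.** The last three rows come from simulation with 2,000,000 draws.

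| Sample | One sex (girls in the simulation) | 80% girls |
|---|---|---|
| Ages 8-17, entry visit | 0.93 | 0.89 |
| Ages 10-14 (SD 4/√12 = 1.155) | 0.75 | 0.665 |
| Peak inside a two-year window, entry visit | 0.49 | 0.40 |
| Peak inside a two-year window, five visits pooled | 0.67 | 0.58 |
| Entered before peak, all visits to age 18 | 0.93 | 0.88 |

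About 22% of patients have their peak inside a two-year window, that is 5 to 6 of the 25 in the first analysis. Among them, age correlates 0.87 (girls) or 0.91 (80% girls) with age at peak, although the correlation is zero in the full simulated cohort. Selection alone produces it.

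**4. A perfect maturity marker against age at peak.** If the marker equals time to peak exactly and visit age is not adjusted for, r = 1.020/2.791 = 0.37. It fails the rule.

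**5. Parts of height.** For parts with SDs s1 and s2 and correlation ρ, r(part 1, sum) = (s1 + ρ·s2)/√(s1² + s2² + 2ρ·s1·s2).
- Equal SDs, ρ = 0: both 1/√2 = 0.707.
- SD ratio 1.5, ρ = 0: 0.83 and 0.55.
- Equal SDs, ρ = 0.3: both 0.81; ρ = −0.1: both 0.67.

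Whenever ρ ≥ 0, the part with the larger SD reaches at least 0.707. This concerns the size of simultaneous growth, not its timing.

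**The case against.** The strongest reply has three parts.

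**The rule is modest and is not the only analysis.** Confidence intervals accompany each coefficient, and the predictive equations come from multiple regression. This is true, but the intervals describe sampling error around the same quantity, and the regression does not replace the single correlations offered to clinicians.

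**The 0.93 is conditional.** This stands. It needs uniform ages, one sex, time to peak and known peaks. Age is named as a component of maturity in the Background but is absent from the Outcome measurements list, and Figure 5 is not shown, so age is a benchmark and not shown to be a tested indicator. In the first analysis it would fail 0.70 against time to peak (0.40 to 0.67). That instability is itself the argument against a fixed cutoff.

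**A condensed article need not list covariates.** This also stands, and it limits what may be concluded. A reader might infer that the sexes are pooled or that sex is left out of the model; the article states neither. A reader might infer that 0.70 decides which indicators enter the algorithm; no section says so. A reader might infer that menarche or breast stage not yet reached would be imputed; the missing-data paragraph speaks only of a single parameter missing at an attended visit. Nor does the article say that height, sitting height and leg length will all enter one regression, so a singular model is only a possibility.

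**Conclusion.** The concern holds for the stated rule. An unadjusted correlation above 0.70 does not show that an indicator predicts timing in the individual patient. Over ages 8-17, with the assumptions listed, it is compatible with ±3.9 years, about twice the ±2.0 years that the protocol already rejects and that age alone achieves at about 0.93 (0.89 with 80% girls). The exact figures rest on assumed age distributions and sex mix. The conclusion does not: the coefficient's meaning varies with the sample, and the outcome it refers to is not fixed. No comparable figure can be given for curve progression, because the article states no SD for it.

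The part-whole point is narrower. It would be tempting to say that both parts of height pass 0.70 by construction; that needs equal variances and no correlation between them. What is guaranteed is that at least one part reaches 0.707 with concurrent height velocity when the parts are not negatively correlated.

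**What to change.** Change the statistical section as follows.

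1. State the outcome of each correlation: age at peak, time to peak, magnitude of the peak, or curve progression over a named interval.
2. Replace the 0.70 criterion with each indicator's added value over chronological age and sex (partial correlation or added R², with confidence interval), together with the prediction error in months for time to peak and in degrees for curve progression.
3. Take predictor values from a visit before the interval being predicted.
4. Do not judge sitting-height or leg-length velocity by its correlation with height velocity over the same interval. If these measures enter one regression, use at most two of height, sitting height and leg length.

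The cost is wording and slightly more analysis. Age and sex are basic details of routine care, so no new measurement is needed. A model with age, sex and one indicator has three terms, fewer than the 4-5 predictors for which the sample size was checked. The coefficients will look less favourable than unadjusted ones.

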**Figure 5 F5:**
[figure not shown]
**Correlations investigated in this study**.

Multiple linear regression analysis of the data is used to determine predictive equations for the timing and magnitude of the peak growth velocity of height, and the scoliotic curve progression.

Missing data concerning individual parameters are not expected in this study. I.e. when a patient misses his or her follow up consult, *all *parameters will be missing and therefore no correlations can be calculated for that time point. It is not expected that when a patient does come to the outpatient clinic, for example the sitting height will not be measured and all the other parameters will be measured. If it does happen anyway that one individual parameter is missing, imputation techniques will be applied during data analysis.

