The goal of this study is to determine the predictive value of several maturity indicators that reflect growth or remaining growth potential, in order to predict timing of the peak growth velocity of total body height in the individual patient with adolescent idiopathic scoliosis. Furthermore, different parameters are evaluated for their correlation with curve progression in the individual scoliosis patient. An algorithm is made for determining the optimum treatment strategy in the individual patient with adolescent idiopathic scoliosis.

A description of the maturity indicators is presented below.

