### Study protocol

The study protocol will be incorporated in the usual care of patients visiting the outpatient clinic for follow up of adolescent idiopathic scoliosis. Follow up will take place every six months. Patients will be followed until 18 years of age or until growth of the spine has stopped and skeletal maturity has been reached. Furthermore, patients will be lost to follow up when they receive surgical treatment.

A description of the (follow up) consult is presented below.

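### For time-varying indicators against curve progression, the plan names only Pearson correlations, apparently run visit by visit, and ordinary linear regression, with no unit of analysis and no allowance for repeated visits per child

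*Protocol article*

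**What the plan says.** All references are to the protocol article.

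- **Study protocol** sets the schedule: "Follow up will take place every six months". **Outcome measurements** opens its list with "Longitudinal data will be acquired for". The list includes curve progression, body lengths and their velocities, Tanner stage, Risser sign, skeletal age and EMG ratios.
- **Sample size and statistical analysis** sets the first analysis: "We aim to perform a first preliminary analysis of the longitudinal data when patients have a follow up of at least 2 years". It expects complete data on at least 25 patients. It names Pearson correlations of each parameter with the peak growth velocity and with curve progression, treats a value above 0.70 as clinically relevant, and promises confidence intervals so that this value can be interpreted reliably.
- The same section, after Figure 5, adds the regression: "Multiple linear regression analysis of the data is used to determine predictive equations for the timing and magnitude of the peak growth velocity". The sentence then extends to curve progression. It does not say what one row of data is.
- The missing-data paragraph that follows says that after a missed consult "no correlations can be calculated for that time point". This is the only indication of the level at which correlations are run.
- **Background** gives the aim: to "predict timing of the peak growth velocity of total body height in the individual patient". The Abstract (Methods/design and Discussion) likewise relates the indicators to the timing of the growth spurt, whereas the statistical section and the closing Discussion refer only to the peak growth velocity.

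**The concern.** Curve progression and most of the maturity indicators are measured repeatedly in the same child. Pearson correlation and ordinary multiple regression treat every row as a separate subject. No patient effect, clustered standard error, one-summary-per-patient rule or alignment of visits on maturity is named.

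For these repeated pairs two ways of following the text suggest themselves, and both are unsatisfactory.

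- **Visit by visit**, as the missing-data paragraph implies. Each coefficient uses one row per child, so its interval is valid for that visit. But each indicator then gets four or five separate coefficients with no rule for combining them, and visit number says little about where a child stands relative to the growth spurt.
- **Pooled**, with all intervals in one table. The rows are not independent, and the intervals come out too narrow.

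The confidence intervals are what the plan relies on for judging whether an indicator reaches the 0.70 threshold, and the results are meant to feed a treatment algorithm. An interval that is too narrow makes an indicator look better established than 25 children can show.

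**Working it through.** **Inputs from the article.** Accrual 60 per year; 30 patients with two years of follow-up at 2.5 years; 25 analysable; visits every 6 months; relevance threshold r = 0.70; entry age 8 to 17 years; peak growth at 10 to 14 years in 95% of girls.

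**Assumed.** 95% confidence level; within-patient correlation (ICC) of 0.2, 0.5 or 0.8, because the article gives none.

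**1. The plan's own count.** Patients enrolled in the first half-year reach two years by 2.5 years: 60 × (2.5 − 2) = 30. This agrees with "As the expected number of new patients is 60 each year" and "it will take 2.5 years for 30 patients to reach a follow up of at least 2 years". Going from 30 to 25 implies a loss of 5/30 = 16.7%. The count is of patients, not visits.

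**2. Rows available.** Two years at six-month spacing gives 5 visits and 4 intervals. Twenty-five patients give 25 × 4 = 100 interval rows. One visit-level analysis of progression uses 25 of them, a quarter.

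**3. Interval for r = 0.70.** Fisher z: tanh(atanh(0.70) ± 1.96/√(n − 3)), with atanh(0.70) = 0.867.

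| Rows treated as independent | 1.96/√(n − 3) | 95% CI |
|---|---|---|
| 25 | 0.418 | 0.42 to 0.86 |
| 100 | 0.199 | 0.58 to 0.79 |

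Pooling cuts the width from 0.44 to 0.20. The 25-patient interval is the bounding case, in which further visits add no information. Depending on the ICC, a correct repeated-visit interval lies between the two.

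**4. Size of the error between those bounds.** With m = 4 intervals, the design effect is 1 + (m − 1) × ICCx × ICCy when both variables vary within patient, and 1 + (m − 1) × ICC when one is constant within patient. The standard error is understated by the square root, and the effective n is 100 divided by the design effect.

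| ICC (assumed) | Both vary: design effect | SE factor | Effective n | One constant: design effect | SE factor | Effective n |
|---|---|---|---|---|---|---|
| 0.2 | 1 + 3 × 0.04 = 1.12 | 1.06 | 89 | 1 + 3 × 0.2 = 1.6 | 1.26 | 62 |
| 0.5 | 1 + 3 × 0.25 = 1.75 | 1.32 | 57 | 1 + 3 × 0.5 = 2.5 | 1.58 | 40 |
| 0.8 | 1 + 3 × 0.64 = 2.92 | 1.71 | 34 | 1 + 3 × 0.8 = 3.4 | 1.84 | 29 |

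The left half applies to a changing indicator against interval progression. The right half applies when, for example, an outcome fixed for each child is repeated over visits. These factors are derived for no true association and are approximate at r = 0.70. As a check, a simulation of pooled Pearson tests with 25 patients, 4 rows each and both ICCs at 0.5 rejected a true null in 13.6% of 8,000 runs at a nominal 5%. The formula predicts 2 × [1 − Φ(1.96/1.32)], about 14%.

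**5. What visit number groups together.** Suppose entry age is uniform on 8 to 17 years and age at peak is 12 years with SD 1 (the girls' range). Time from peak at any given visit then has variance 9²/12 + 1² = 7.75, so SD 2.8 years. About (17 − 12)/9 = 56% of children are already past the peak at visit 1. The uniform entry age is an assumption. The point is only that a visit number mixes children several years apart in maturity.

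**The case against.** The strongest reply is that a third reading exists: one row per patient. Timing and magnitude of peak height velocity occur once per child, and the sample size is counted in patients throughout. A regression with one row per child has neither problem, and its interval at n = 25 is the correct one. The regression sentence names no row unit, the per-time-point reading rests on one remark about missed consults, and Figure 5 is not shown. This stands for peak velocity. It does not settle curve progression, which recurs over every interval. Even for peak velocity, it leaves open which visit's Risser, Tanner or EMG value enters the model.

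Three stronger inferences are tempting, and the article does not support them.

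- *The published intervals will be wrong.* No passage says that visits are pooled, so the 100-row interval shows what would happen, not what is planned.
- *The correlations target the magnitude of the peak, although the aim is its timing.* The Abstract says twice that indicators are related to timing, and the regression covers timing explicitly. The statistical section is loosely worded and needs aligning.
- *A perfect maturity clock would show no linear correlation, because velocity rises and then falls.* That concerns current height velocity, which the plan only plots. The stated correlations are with peak velocity and curve progression.

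A spread of ages at one visit is also not an error in itself, since relating maturity to time-to-peak needs such a spread. What remains is that visit number is an uninformative way to divide repeated data on progression.

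Finally, an article may leave covariance details to a fuller document. But this one names its methods and implies the level at which correlations are run. As stated, those methods do not fit repeated outcomes.

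**Conclusion.** The point holds in a limited form. For time-varying indicators against curve progression, the named methods either divide about 100 intervals into visit-level sets of 25 or, if visits were pooled, overstate precision. In the pooled case the interval for r = 0.70 would be 0.58 to 0.79, against a patient-only bound of 0.42 to 0.86. Standard errors would be understated by about 1.06, 1.32 or 1.71 times at assumed ICCs of 0.2, 0.5 or 0.8 in both variables, and by up to 1.26, 1.58 or 1.84 times when one variable is constant within patient.

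The size depends on the ICCs, which the article does not give, and on a choice of row unit that it does not state. For timing and magnitude of peak velocity, a sound one-row-per-patient analysis is compatible with the text and only needs to be written down. The change should be made because it is cheap and because the results are intended to guide treatment decisions.

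**What to change.** 1. **Curve progression.** State one row per six-month interval. Regress the Cobb change over the next interval on values known at its start, in a linear mixed model with a patient random intercept, or by GEE.
2. **Correlations that use repeated visits.** Take the confidence intervals from a bootstrap that resamples patients, not visits.
3. **Timing and magnitude of peak height velocity.** Keep one row per patient, with predictors taken at a pre-stated landmark such as the first visit. Either restrict to children whose peak is observed or treat the others as censored. A random-intercept model for years-to-peak is not a substitute: that outcome falls by exactly 0.5 per visit in every child, so it would reward any indicator that rises with time, and it is unobserved when the peak lies outside follow-up.
4. **Wording.** Align the statistical section with the Abstract, so that timing of the peak is named as the correlation target.

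**Cost.** The change needs no new measurements and alters no stated figure. The output becomes slightly more complex, and intervals will be wider than a pooled analysis would give. Item 3 may reduce the number of children contributing an observed peak at the first analysis, and that number should be reported.
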